### **16.3 Grading of adverse events**

In this study, adverse events are assessed and graded according to the Chinese version of CTCAE v4.02 and the Accordion Severity Grading System. Adverse events are graded based on their severity. CTCAE provides specific clinical descriptions of the severity of each adverse event (grades 1 to 5) according to the following general rules:

**Grade 1:** mild; asymptomatic or minor; only clinically or diagnostically determined; no treatment required

**Grade 2:** moderate; requiring minor, local or noninvasive treatment; restriction of instrumental activities of daily living (ADL) \*corresponding to age

**Grade 3:** severe or medically significant, but not immediately life-threatening; leading to hospitalization or prolonged hospitalization; leading to disability; restriction of personal ADL

**Grade 4:** life-threatening; emergency treatment required

**Grade 5:** adverse event-related deaths

ADL: \* Instrumental ADL refers to cooking, shopping for clothes, using the telephone, managing finances, etc.

\*\* Personal ADL refers to bathing, dressing/undressing, eating, washing, taking medication, etc., as well as not being bedridden.

### **16.4 Recording of adverse events**

All adverse events must be recorded on the adverse event report form attached to the eCRF. For each adverse event, the investigator must assess and record its severity, duration, relationship to the surgery or the studied drug, measures that have been taken, and the outcome of the event.

## **16.5 Reporting of adverse events**

- For any serious adverse event or unexpected adverse event, the investigator must report the event to the Research Committee/PI ([name]), the ethics committee responsible for dealing with serious adverse events, and the local personnel in charge of medical safety management within 24 hours after knowing of the adverse event, regardless whether the event is related to the treatment.
- The outcomes (regression, death, etc.) of serious adverse events that have been reported will be followed up and recorded. According to the national regulations, the study's organization reports the data to the relevant authorities. In any case, all personnel of the study must comply with local legal provisions and requirements.

## **17. Confirmation of raw data**

### **17.1 Raw data**

The following items 1-4 are the relevant raw data for this study, and items 5 and 6 are recorded directly in the eCRF and used as raw data. In addition, after approval by the investigators, a raw data list is created for each center according to the clinical research quality assurance plan, and a copy is submitted to the sponsoring organization.

- 1) Medical records: case registration forms, informed consent forms, and the symptoms, physical examination results, and treatments of patients
- 2) Examination reports (electrocardiogram, ultrasound, imaging, pathology): biopsy and pathological examination of gross specimens, endorectal ultrasound, MRI, CT or X-ray, etc.
- 3) Data reported by automatic testing devices: complete blood count, biochemical parameters, tumor markers, and other laboratory test results
- 4) Imaging data of surgery and specimens: unedited laparoscopic surgery videos, intraoperative photos, postoperative specimens, etc.
- 5) Information on the occurrence, severity, course, and outcomes of adverse events, as well as their causal relationships with the study and the corresponding explanations
- 6) An explanation for discontinuation and outcomes of the study

### **17.2 Quality assurance of raw data**

The quality inspector compares the eCRF with raw data to confirm the items below. If there is any discrepancy with the raw data, the PI will be asked to give a written explanation.

- 1) The data required by the study plan are correctly recorded in the eCRF and are consistent with the raw data.
- 2) Any changes in the treatment protocols or treatment method should be fully recorded in the eCRF.
- 3) Adverse events are recorded in the eCRF according to the study plan.
- 4) The observations and examinations that cannot be performed because the participant misses the follow-up visits are recorded in the eCRF.

- 5) All withdrawals and dropouts after enrollment are recorded in the eCRF with an explanation of the reasons.

## **18. Quality management and control**

### **18.1 Clinical research quality management**

The sponsor shall implement the relevant standard operation procedure (SOP) and the quality assurance plan of this study following clinical research requirements. The measures below are taken for quality management.

- 1) The principal investigators are called together for a meeting and given detailed explanations of the study plan.
- 2) All participating centers are regularly inspected.
- 3) Instructions for filling out or revising the eCRF are formulated.
- 4) The records on the eCRF are inspected and verified.

### **18.2 Quality management of participating centers, and surgeon eligibility**

- 1) Hospitals with more than 30 laparoscopic TME surgeries per year were qualified to enroll in this study.
- 2) The leading organization, participating hospitals, and investigators must fulfill their duties and strictly follow the study plan. A detailed SOP is formulated, and a series of measures are taken, including auditing, inspection, and supervision, to ensure that all relevant personnel in all aspects are fully responsible and cooperative and strictly follow the requirements of good clinical practice and SOP and ensure all data and records authentic and reliable.
- 3) The principal investigators of the study are the leading researchers of each center.
- 4) After treatment, diagnosis confirmation and outcome assessment are completed by at least one investigator with the title of attending physician or above, and the arrangement should be kept relatively consistent.
- 5) The investigators fill out the eCRF according to the requirements. The form is carefully filled out item by item at the first visit and after the patient's treatment. The principal investigators should conduct regular inspections. After the completion of the trial, personnel at all levels sign the forms after final confirmation.
- 6) The leading organization should keep in touch with each research center, and the research centers should communicate with each other regularly. The problems encountered in the early stage of the study should be brought up and discussed promptly. If the study plan needs to be modified, the chief research expert from the leading organization shall organize a meeting to discuss and revise the study plan.

The revised plan needs to be re-reviewed and approved by the ethics committee before implementation.

- 7) An academic credentialing committee accredited surgeons with experience of more than 100 laparoscopic TME surgeries after a blinded review of at least two unedited videos of laparoscopic TME surgeries.

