## **10. Pathological assessment**

### **10.1 Macroscopic assessment of mesorectal excision**

The quality of TME is assessed using a central pathological evaluation method, which is a double-blinded evaluation by two experienced pathologists based on photographs of fresh specimens. According to the evaluation criteria proposed by Nagtegaal et al., the quality of TME is classified into three levels as follows:

**(1) Complete:** the mesorectum is intact and has a smooth surface with very few irregularities; no defect more than 5 mm in depth; no coning of the distal margin of the specimen; the upper circumferential resection margin (CRM) appears smooth and flat in the slices of the specimen.

**(2) Nearly complete:** the mesorectum is almost intact, but its surface is irregular; the distal part of the specimen shows moderate coning; the muscularis propria is absent except for the level where the levator ani muscle is inserted; the upper CRM appears moderately irregular in the slices of the specimen.

**(3) Incomplete:** the mesorectum appears incomplete with defects deep into the muscularis propria, and/or the CRM is extremely irregular.

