### **10.2 Microscopic pathological examination**

The local pathologists did the microscopic pathological assessments at the participating centers. Positive resection margin, including circumferential resection margin (CRM) and distal resection margin (DRM), was defined as the presence of cancer cells within 1 mm from the cut edge.

- Pathohistological type and tumor differentiation
- Distance of surgical resection margins (proximal, distal, and circumferential)
- Positivity of surgical resection margins (proximal, distal, and circumferential)
- Numbers of dissected lymph nodes
- Numbers of metastatic lymph nodes
- Tumor regression grade (TRG) in patients undergoing preoperative chemoradiotherapy
- pTNM or ypTNM stage

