#### **11.1.9 Unblinding**

This study is an open-label trial that does not involve unblinding or emergency unblinding.

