### 18.3 Surgical quality management

- 1) If the anal sphincter is preserved or partially preserved, the distance (cm) between the anastomosis and the anal verge must be recorded after the operation.
- 2) Surgical imaging data: The unedited video of each laparoscopic surgery is saved and backed up to the sponsoring organization for unified storage within 12 months after surgery. The Academic Credentialing Committee conducts a review and monitoring of the surgical quality of laparoscopic surgery per 6 months.
- 3) Intraoperative photographs: The images showing the dissection of the No. 253 lymph nodes are routinely collected during surgery using a digital camera with 8 million or more pixels or a laparoscopic surgery video-recording system (**Fig. 1**).
- 4) Postoperative specimen photographs:
  - After the surgical specimen is taken out of the body, the integrity of the mesorectum is checked and photographed by a digital camera with 8 million pixels (**Fig. 2**).
  - Cut the intestinal wall along the anterior wall of the rectum and avoid the lesion. The mucous membrane of the cut specimen was placed upward on a plate or similar object, which was stretched and fixed in a nearly physiological state, and photographed (placed with a ruler), measured, and recorded (**Fig. 3**).
- 5) Data recorded: the distance between the upper margin of the tumor and the opening-side margin of the resected rectum, the distance between the lower margin of the tumor and the anus-side margin of the resected rectum (or the resected skin margin), the size of the tumor, and the ratio of the maximum diameter of the tumor to the transverse diameter of the intestinal canal.
- 6) **Numbering of surgical and specimen imaging data:** The video of the laparoscopic surgery is given the same number as **the patient's randomization number**. The intraoperative photos showing the dissection of the No. 253 lymph nodes and postoperative specimen photos are numbered as the participant's randomization number plus Fig. 1, Fig. 2, or Fig. 3. For example, the photos of patient 001 are numbered 001 Fig. 1, 001 Fig. 2, and 001 Fig. 3 accordingly.

- 7) The intraoperative photos showing the dissection of the No. 253 lymph nodes and postoperative specimen photos are uploaded to the EDC system within one week after surgery.

[figure not shown]

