| Other cancer treatments (e)                            | Record when it occurs  |       |   |   |    |    |    |    |    |             |

Note:

(a) If the patient shows signs of tumor recurrence (e.g., clinical symptoms), additional tumor assessment is required. All assessments to confirm the recurrence/new onset of tumors should be recorded in the eCRF, including tumor assessments not included in the study plan.

(b) MRI or CT: The use of oral or intravenous contrast agents should be kept as consistent as possible. The same investigator or radiologist assessed each patient's scan results as consistently as possible during the study.

(c) Patients whose preoperative fiberoptic colonoscopy did not pass the lesion should undergo the fiberoptic colonoscopy three months after surgery.

(d) Tumor recurrence and the survival of patients are followed up until death. The last known survival date or data from the last two years were used for the analysis of patients who survived.

**(e) Other cytotoxic agents, drugs to be studied, and active or passive immunotherapy for rectal cancer are not allowed during the treatment or follow-up period without tumor recurrence.**

(f) The examinations can be done within  $\pm$  four weeks of the planned date, but the 6-month tumor assessment must be done after the treatment of all studied drugs is completed.

(g) The examinations are done once every six months. Fiberoptic colonoscopy is done once a year and again within one year if any abnormality is detected. Fiberoptic colonoscopy is done again within three years if no polyps are found and then once every five years. It is recommended that colorectal adenomas found in follow-up examinations be surgically removed.

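### No masking is stated for the readers of recurrence, margins or node counts, and the photographs for the blinded TME grade carry a linkable number; both can be tightened at low cost

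*Combined protocol and SAP*

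**What the plan says.** The protocol (section 4) and the SAP (section 3) describe an open-label noninferiority trial. Protocol section 11.1.9 adds: "This study is an open-label trial that does not involve unblinding or emergency unblinding". The primary outcome is the 3-year DFS rate. Under section 8.4.1 a recurrence is dated at definitive diagnosis and needs support from imaging or pathology, and death from any cause also counts.

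On who judges the outcomes:

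- **Recurrence.** Section 18.2 item 4: after treatment, "diagnosis confirmation and outcome assessment are completed by at least one investigator with the title of attending physician or above". Appendix 2, follow-up schedule, note (b): "The same investigator or radiologist assessed each patient's scan results as consistently as possible during the study".
- **Margins and nodes.** Section 10.2: "The local pathologists did the microscopic pathological assessments at the participating centers". A margin is positive if cancer cells lie within 1 mm of the cut edge.
- **TME grade.** Section 10.1: a central, "double-blinded evaluation by two experienced pathologists based on photographs of fresh specimens".

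On how the images are filed, section 18.3 item 6 says: "The video of the laparoscopic surgery is given the same number as" the patient's randomization number. The photographs carry that number plus a figure suffix, with patient 001 as the example. Fig. 1 is the intraoperative picture of the node dissection, taken "using a digital camera with 8 million or more pixels or a laparoscopic surgery video-recording system" (item 3). Figs. 2 and 3 show the specimen (item 4). Section 9.1 has the same number written into the study medical record.

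**The concern.** The operating team cannot be masked in a surgical trial, but the people who read scans, slides and photographs often can be. Here the text leaves the first two groups free to know the arm. Nothing stops the confirming investigator from having been on the patient's operating team, although nothing says that this happens.

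In a noninferiority trial, recurrences that are missed or dated later in the experimental arm reduce the observed difference and make the noninferiority claim easier to reach. The objective-evidence rule guards against false recurrences more than against late or overlooked ones. Some room for timing remains. Cross-sectional imaging is yearly (section 7), visits may fall four weeks either side of the planned date (Appendix 2, note (f)), and a recurrence is dated when it is confirmed. A diagnosis near 36 months can therefore fall on either side of the 3-year cut.

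For TME grade the question is narrower: whether a file number shared with the operative video weakens a blind that the plan has already chosen to have.

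**Working it through.** **Step 1: is any reader masked?**

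- Recurrence (18.2 item 4; Appendix 2 note (b)): no masking stated, and no masked adjudication described.
- CRM, DRM and node counts (10.2): no masking stated.
- TME grade (10.1): blinded, though what the raters are blind to is not spelled out.
- Surgeon accreditation videos (18.2 item 7): blinded review, but this is not an outcome.
- SAP: no text on masking of assessors.

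TME grade is therefore the only outcome with a stated blind.

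**Step 2: does the file number reveal the arm?** The example number has no arm code. It becomes informative only if a rater can link it to the laparoscopic video, the intraoperative Fig. 1 or the medical record. Section 10.1 bases grading on specimen photographs, and no section says that the raters receive Fig. 1. Pathologists are not among the EDC users named in section 11.1.3. No recoding before the central reading is described either. Linkage is possible but not shown.

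**Step 3: what size could differential ascertainment have?** The plan has no figure to reproduce, because masking does not enter its sample-size calculation. The inputs from protocol section 5 are open-arm 3-year DFS of 94.3% (stage I, 359 patients) and 75.2% (stage II/III, 609 patients), 646 laparoscopic and 322 open patients, a 10-point margin and one-sided α of 2.5%. The share f of laparoscopic events missed or dated after 3 years is an assumption, 5-10%.

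Pooled DFS at the planned stage mix = (359 × 94.3 + 609 × 75.2) / 968 = 82.3%, so 17.7% have events.

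Shift in the difference = (1 − DFS) × f, taking the same true event rate in both arms:

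- Stage I: 5.7 × 0.05 = 0.3; 5.7 × 0.10 = 0.6 points
- Stage II/III: 24.8 × 0.05 = 1.2; 24.8 × 0.10 = 2.5 points
- Planned mix: 17.7 × 0.05 = 0.9; 17.7 × 0.10 = 1.8 points

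These are upper values for a given f, because f is applied to all events and deaths are not open to a reader's judgement. The documents do not split recurrences from deaths, so the reduction cannot be computed.

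**Step 4: effect on the one-sided error.** This uses a normal approximation for the difference in 3-year DFS, with the true difference at the margin (open 82.3%, laparoscopic 72.3%).

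SE = √(0.723 × 0.277 / 646 + 0.823 × 0.177 / 322) = 2.8 points.

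Error with a hidden shift b = P(Z > 1.96 − b/SE), with the SE recomputed for each b:

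- b = 0: 2.5%
- b = 0.5 points (about 3 laparoscopic patients): 3.8%
- b = 1 point (about 6 patients): 5.5%
- b = 2 points (about 13 patients): 11.0%

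At the margin the laparoscopic event rate is 27.7%, so 1 point is 1 / 27.7 = 3.6% of that arm's events. If only 80% of patients are evaluable, the last two errors are 5.1% and 9.6%. This approximates the planned survival analysis and does not reproduce it.

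**The case against.** The strongest reply has four parts.

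- **The trial is openly unmasked and has safeguards.** Recurrence needs imaging or pathology, death from any cause counts, margin positivity has a numeric rule, and margins are secondary outcomes. Section 7 and Appendix 2 fix the same surveillance for both arms, and note (a) makes further assessment mandatory when signs of recurrence appear. This stands, and it limits the bias. It does not remove judgement about an equivocal scan or the date of confirmation.
- **The TME blind may be sound.** A reader might infer from the shared number, or from Fig. 1, that the blind is broken. The documents do not support that. The number has no arm code, grading rests on specimen photographs, and the randomization tables are kept sealed (9.1). This stands; only a linkage risk remains.
- **The direction is not known.** A reader might infer that investigators who are experienced laparoscopic surgeons would favour their technique. Section 18.2 accredits surgeons on laparoscopic experience but requires only attending grade of the outcome assessor, and it says nothing about motive. Closer scrutiny of the laparoscopic arm would bias the other way. This stands.
- **The remedy masks imperfectly.** Scars, CT appearances and chart access can reveal the approach, and a second attending at the same site may know the arm. This stands too, and it is why the second-attending rule is only a preference below.

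The protocol also refers to a detailed SOP that is not among the documents. If masking is written there, the point reduces to citing it.

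**Conclusion.** The point holds as a low-cost improvement. No masking is stated for those who determine recurrence, margins or node counts, so differential ascertainment is possible and the plan limits it only indirectly. The label on the TME photographs is a linkage risk, not a demonstrated break.

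The size is an assumption throughout. With 5-10% differential under-detection in the laparoscopic arm, the shift is about 0.9-1.8 points at the planned stage mix, and less once deaths are excluded. Quoting only the 1.2-2.5 points of stage II/III would present the stratum with the larger shift as if it were the whole trial. Step 4 shows that even a 1-point shift would matter if it occurred; it does not show that it would occur. Neither the rate nor the direction comes from the documents.

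A reader might also infer that masking is practically free. The documents give no costs. Low cost is a fair judgement for request forms and file recoding, but less certain for confirming recurrence, where an existing assessor may already know the operation.

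**What to change.** 1. **Appendix 2, note (b):** have follow-up scans read by the existing site radiologist, from a request form that omits arm and operative route. The type of resection can still be stated, since the same resections are used in both arms.
2. **Section 10.2:** use a pathology request form that omits the surgical approach.
3. **Sections 10.1 and 18.3:** give the central TME raters only the specimen photographs (Figs. 2 and 3), under a separate random code. State that the raters are blind to arm and do not see the randomization number.
4. **Section 18.2 item 4:** where a site has a second attending, recurrence should preferably be confirmed by one who was not on that patient's operating team. This should not be mandatory, because it may strain small sites and does not itself mask.

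The cost is a change of wording, two neutral forms and recoding of image files. Items 1 to 3 need no extra readers, scans or procedures, and sample size and α do not change. Masking will remain imperfect for the reasons given above, and the report should say so.

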### 18.3 Surgical quality management

- 1) If the anal sphincter is preserved or partially preserved, the distance (cm) between the anastomosis and the anal verge must be recorded after the operation.
- 2) Surgical imaging data: The unedited video of each laparoscopic surgery is saved and backed up to the sponsoring organization for unified storage within 12 months after surgery. The Academic Credentialing Committee conducts a review and monitoring of the surgical quality of laparoscopic surgery per 6 months.
- 3) Intraoperative photographs: The images showing the dissection of the No. 253 lymph nodes are routinely collected during surgery using a digital camera with 8 million or more pixels or a laparoscopic surgery video-recording system (**Fig. 1**).
- 4) Postoperative specimen photographs:
  - After the surgical specimen is taken out of the body, the integrity of the mesorectum is checked and photographed by a digital camera with 8 million pixels (**Fig. 2**).
  - Cut the intestinal wall along the anterior wall of the rectum and avoid the lesion. The mucous membrane of the cut specimen was placed upward on a plate or similar object, which was stretched and fixed in a nearly physiological state, and photographed (placed with a ruler), measured, and recorded (**Fig. 3**).
- 5) Data recorded: the distance between the upper margin of the tumor and the opening-side margin of the resected rectum, the distance between the lower margin of the tumor and the anus-side margin of the resected rectum (or the resected skin margin), the size of the tumor, and the ratio of the maximum diameter of the tumor to the transverse diameter of the intestinal canal.
- 6) **Numbering of surgical and specimen imaging data:** The video of the laparoscopic surgery is given the same number as **the patient's randomization number**. The intraoperative photos showing the dissection of the No. 253 lymph nodes and postoperative specimen photos are numbered as the participant's randomization number plus Fig. 1, Fig. 2, or Fig. 3. For example, the photos of patient 001 are numbered 001 Fig. 1, 001 Fig. 2, and 001 Fig. 3 accordingly.

- 7) The intraoperative photos showing the dissection of the No. 253 lymph nodes and postoperative specimen photos are uploaded to the EDC system within one week after surgery.

[figure not shown]

